### Measurements

Participants go through a battery of tests before the intervention (Fig. 3), 3 months and 6 months into the intervention and after the intervention. Additionally, follow-up testing is performed at 2, 5 and 10 years after the intervention. Follow-up testing is deemed critical because it may allow us to discover long-term beneficial or detrimental effects of these interventions. In the section below we will go through the different data modalities that will be gathered as part of the intervention and the rationale for why these measures were chosen. Tests are performed according to defined standard operating procedures (SOPs) in the same order for all participants at all visits, and to ensure a minimum of bias, test leaders are instructed to not look at the participants’ previous test results before a new test. In addition, biological samples will be processed using harmonized workflows with batch tracking, internal controls, and standardized normalization procedures where applicable. For molecular analyses, raw data and metadata will be retained to allow reprocessing and harmonized downstream analyses as analytical methods evolve. For phenotypic and physiological measurements, personnel will be trained in predefined acquisition procedures to minimize interoperator bias.

**Fig. 3 Fig3:**
[figure not shown]
Visualization of the test-battery. **A**. Participants are tested at baseline, after 3 months, 6 months and 1 year, and follow-up will be performed 2, 5 and 10 years after baseline. **B**. A stool sample is collected at home for microbiome analysis within 18 hours of the test day and brough to the lab. A blood sample is collected to assess multiple blood markers after which participants fill out questionnaires, have their blood pressure measured and a digital photo is taken and a voice recording ise performed. Body composition is measured with a DXA scan and VO_2_max is estimated with Seismofit. Lastly participants perform a physical test battery consisting of handgrip strength, gait speed and sit-to-stand tests as well as a graded cardiopulmonary VO_2_peak test

#### Primary outcome measure

As the primary outcome measure of the trial, Dunedin Pace of Aging DNA methylation analyses (Belsky et al. 2020) will be performed using the Illumina 450 K array on peripheral blood mononucleated cells. It was chosen to isolate these cells instead of performing investigations on whole blood to reduce the potential effect of blood composition changes that may be a side effect of interventions. Raw DNA methylation data will be stored to enable re-analysis using both current and future generations of epigenetic clocks and computational pipelines. Long-term follow-up samples will initially be analyzed using the same methylation platform and primary clock algorithms to ensure longitudinal consistency, while harmonized re-analysis with updated methods may subsequently be performed as the field evolves. In addition, specific DNA methylation changes in the epigenome will be investigated in secondary explorative outcomes in connection with RNA-sequencing results with appropriate false discovery rate corrections made.

#### Exploratory outcome measures

Blood work

Venous blood is collected following a 12-h overnight fast at the start of the test day and used for analysis of multiple parameters (Table 1).

**Table 1 Tab1:** Measured blood markers

Category	Blood marker
Inflammatory markers	TNF-α, IL-6, IL-8, CRP
Glycemic control	HbA1C, Glucose
Hematology	Hb, Erythrocytes, Hct, MCH, MCHC, MCV, Platelets, RBC, Leukocytes, Basophils, Eosinophils, Monocytes, Lymphocytes, Neutrophils
Molecular tests	DNA methylation, RNA-sequencing, Metabolomics
Biochemical	ALAT, ASAT, Alkaline phosphatase, Albumin, Urea, Total protein, Iron, Bilirubin, Lactate acid dehydrogenase, Calcium, Creatinine, Total cholesterol, HDL, LDL, Triglycerides, Selenium, Q10, NAD +, Sodium, Potassium, Chloride
Computational tests	Senescence prediction on blood smears (Teklu et al. 2025; Heckenbach et al. 2022)

Measurement of inflammatory markers is important, as chronic, low-grade inflammation is a hallmark of aging and has been linked to an increased risk of frailty and mortality (Flanagan et al. 2020; Arosio et al. 2023; Ferrucci and Fabbri 2018). Glycemic control markers are measured because impaired glucose regulation is common among older adults (Dubowitz et al. 2014) and is associated with elevated risk of most chronic age-associated diseases (Schnell and Standl 2006). Complete blood cell count parameters are assessed since aging influences hematopoiesis, and white blood cell counts serve as predictors of all-cause mortality (Groarke and Young 2019).

RNA-sequencing and DNA methylation changes in blood mononucleated cells will provide insights into transcriptional and signaling processes at the cellular level. Metabolomic profiling will be performed on plasma to assess the changes, exercise and fasting induce at the molecular level and what adaptations and cellular pathways are involved. Lastly, biochemical and metabolic markers are measured to detect organ system decline and age-related metabolic disturbances. Combined with physiological measures this will provide a comprehensive understanding of how fasting and exercise influence aging.

A finger prick is also performed on the tip of the middle finger for thin blood smear senescence prediction as recently described (Heckenbach et al. 2022).

Stool sample

Changes in the gut microbiome have been seen with age and may predict health outcomes in the elderly (Bradley and Haran 2024; N V 2025). Notably, gut microbiome is strongly affected by feeding habits and we expect TRF will have a considerable effect on this (Paukkonen et al. 2024). For that reason, all participants will be given a feces kit to collect a stool sample prior to each test day. The stool sample will be collected on the test day and stored at −80 degrees Celsius until analysis. For analysis, we will perform 16S rRNA sequencing.

#### Questionnaires

To gain understanding of overall health, sleep quality, and cognitive decline participants answer the following questionnaires:

Health examination

Participants will answer a modified version of the Danish Health Examination Survey questionnaire, including questions about chronic diseases, dietary habits, alcohol, stress, physical activity and for female participants their menstrual cycle (see appendix).

Sleep quality

Pittsburgh Sleep Quality Index (PSQI) questionnaire will be used to assess subjective sleep quality and disturbances over the past month. Questions include assessment of duration, latency, efficiency, disturbances, and daytime dysfunction. Sleep will be further evaluated through wearables.

Montreal Cognitive Assessment (MoCA)

The MoCA Full test is performed to assess a wide range of cognitive domains, including memory, attention, executive function, language, visuospatial abilities and orientation, to possibly identify mild cognitive impairment (MCI). This allows for identification of subtle cognitive deficits and is better suited in healthy elderly than the mini-mental state examination (Nasreddine et al. 2005). Nevertheless, several considerations should be made concerning the MoCA test as a secondary outcome. First, the MoCA test may be subject to ceiling effects due to healthy individuals scoring close to max (Bernier et al. 2023), second it is possible that a one-year trial will not yield sufficient changes in MoCA scoring during the trial period (Bernier et al. 2023), third repeat testing may impact the outcome of the test. Nevertheless, we chose this test due to the feasibility in terms of time-management during trial days, the clinical application of test and because we have a significant long-term follow-up time where cognitive decline is expected and where the interventions may impact these outcomes.

#### Vitals

Participants’ resting pulse and blood pressure are measured three times on the left arm using an electric blood pressure monitor in a seated position with both feet flat on the floor and the arm resting on the table. Blood pressure is measured after filling out questionnaires to ensure that the participant is relaxed. Three consecutive readings are obtained automatically, and the mean of the values is used. If the variability between the first three consecutive readings exceeds threshold, the blood pressure measurement is repeated and the outlier is discarded (University of Maryland 2009).

#### Portrait photo and voice recording

A portrait photo as well as a voice recording, answering a standardized question, will be obtained of each participant. For facial photographs, standardized image acquisition procedures will be implemented, including controlled lighting, fixed camera positioning and distance, neutral facial expression, and standardized background conditions. Participants will be instructed to avoid excessive makeup, major facial accessories, and recent cosmetic procedures when possible prior to imaging sessions. Audio clips are expected to be 1 min. Both will be used for determination of the participants’ biological age by using facial image-based and voice-based age prediction algorithms using deep neural networks trained to predict age (Teklu et al. 2025; Kwasny and Hemmerling 2021).

#### Body composition

Body composition and bone mineral density are evaluated with dual energy X-ray absorptiometry (DEXA)-scan (Lunar iDEXA, Madison, Wisconsin, USA) using enCORE software, V.18 (Krugh 2025). A whole-body scan is performed to determine fat-percentage, visceral fat mass, lean body mass and bone mineral density.

#### Handgrip strength

Grip strength is measured to assess the maximal isometric handgrip strength in kilograms with a Jamar Smart Hand Dynamometer (Jamar, Nottinghamshire, UK). Participants are seated in a chair with a straight back with the elbow bent in a 90-degree angle. The dynamometer is pointing vertically upward. The measurement is a 5 s maximum-effort measure and is repeated three times on each hand with one minute rest in between trials on the same hand. The participants are verbally encouraged during each maximum-effort measure. The highest value obtained for each arm is reported and used for data analysis.

#### Gait speed

Participants’ gait speed and function are assessed by a standardized 4-m test, where participants are instructed to walk two times—once at their normal pace and once as fast as they can. Participants are also video recorded while walking and gait speed, acceleration, balance, cadence, step length, posture and joint angles will be estimated using Tracked Biotechnologies’ TrackedGait system (Tracked Biotechnologies, Virginia, USA).

#### Sit-to-stand

A 30 second sit-to-stand test is performed to assess strength in the lower extremities. The test is performed using a chair (45 cm) without armrest. Participants are shown how to perform the test and instructed to place their feet flat on the ground, cross the arms and hold them against the chest. Participants must stand fully and contact the seat fully. The test is completed two times and the score is the highest number of full stands completed within 30 s.

#### ***VO***_***2***_*** measurements***

Estimated VO_2_max

VO_2_max will be estimated at rest using seismocardiographic measurements (Ventriject, Copenhagen, Denmark) (Hansen et al. 2023). This will be done immediately after the DXA scan where participants have been lying down relaxed for ~8-10 minutes.

Direct measure

A cardiopulmonary exercise test (CPET) is performed on a Monark LC7TT bike (Monark, Varberg, Sweden) using the Quark CPET metabolic cart (Cosmed, Rome, Italy) to determine the peak oxygen consumption rate using indirect calorimetry. Participants perform a graded exercise test with warm-up and increment intensity adjusted to their Seismofit-estimated VO_2_max. Estimated peak power output is calculated from the estimated VO_2_max, a sex-specific coefficient, body weight and a regression-based constant interpreted from Eriksen et al (2014). From estimated peak power output, warm-up intensity and increment size are calculated to reach a total test duration of 10–12 min including a 5-min warm up (Buchfuhrer et al. 1983).

#### Activity monitors

Activity monitors (Huawei Band 10, Huawei, Shenzhen, China) will be provided to all participants to monitor daily activity. The activity monitors will be used by EXE and FAX participants to monitor home workouts of self-chosen modality and are used to ensure that average heart rate is > 70% HRmax for each session. For CON and TRF the activity monitors are used to assess average activity level. Furthermore, the monitors are used to assess sleep quality, which will be compared to the PSQI scores.

## Retention

### Biweekly phone calls

To increase participant retention and compliance with the randomly prescribed interventions, personalized attention will be provided through biweekly phone calls throughout the intervention for all four groups. This will give an opportunity to discuss individual challenges and tailor solutions to help participants adhere to the various interventions. However, there will not be applied pressure on individuals to continue their enrollment if they wish to withdraw from the trial.

### Strategy for follow-up assessment

At the end of the study participants will be encouraged to continue with the respective protocols which may allow us to determine differences in health outcomes between individuals that are continuing these behavioral outcomes and those that do not. Participants will be reminded by email ~ 2 months prior to follow-up assessments. The email will be followed up by a phone call shortly after to schedule a date for the follow-up test day. An email with confirmation of the appointment will be sent right after the phone call. A reminder email confirming the agreed time and date will be sent out ~ 2 weeks prior to the follow-up as well as a reminder email with practical information the day before the test day.

### Statistical considerations

Sample size determination for the interventions trial is conducted using the primary outcome DNA methylation measured at 52 weeks for the pooled three intervention groups (EXE, TRF, FAX) versus the control group (Table 2). Biological age prediction using epigenetics yields a standard deviation of ~10% (Guan et al. 2024). Assuming an expected pooled effect size for the intervention groups versus the control group is considerable (Cohen’s d = 1.0). With a probability of a Type I and Type II error set at α = 0.05 and β = 0.20, respectively, the estimated sample size was 40 participants allocated in a 1:3 ratio (controls:intervention groups). Our 3-month pilot study (Slowage, clinical trials id: NCT05593939) as well as a similar previous 1-year training intervention study with older individuals showed low dropout rates around 5–10% (Gylling et al. 2020). To accommodate the possibility of a higher dropout rate, a total of 240 participants will be recruited whereby 60 participants will be included in each of the four groups (EXE, TRF, FAX, CON), allowing for a 33% dropout rate. Data from dropouts will not be included in the primary outcomes but may be used in exploratory outcomes. Statistical analysis of outcomes will be done blinded by the outcome assessor. For omics-derived statistics, such as DNA methylation and transcriptomics, results will be corrected for multiple comparisons using false discovery rate control, for example Benjamini–Hochberg FDR at 5%.

**Table 2 Tab2:** List of outcomes

Procedure	Baseline	3 months	6 months	1 year	Follow-up (2, 5, 10 years)
DNA methylation (primary)	X	X	X	X	X
Questionnaire	X	X	X	X	X
MoCA	X	X	X	X	X
Height	X	X	X	X	X
Weight	X	X	X	X	X
Body composition	X	X	X	X	X
Blood pressure	X	X	X	X	X
Blood samples	X	X	X	X	X
Microbiome sequencing	X	X	X	X	X
Handgrip strength	X	X	X	X	X
Gait speed	X	X	X	X	X
Seismofit	X	X	X	X	X
VO_2_peak	X	X	X	X	X
Voice recording	X	X	X	X	X
Portrait photo	X	X	X	X	X

It should be noted that, although DNA methylation clocks are among the most established biomarkers of biological aging, they remain surrogate measures that may be influenced by technical variation, tissue source, immune-cell composition, and algorithm selection.

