Beyond health benefits, these interventions have economic implications. Given they lower disease burden and subsequently the healthcare utilization, they reduce the financial burden on health systems and extend the productive lifespan of older adults. Research suggests that an increase in life expectancy by 1 year is worth 38 trillion US dollars, while an increase in life expectancy by 10 years is worth 367 trillion US dollars (Scott et al. 2021). Promoting fasting and exercise in elderly populations, therefore, holds potential to generate significant economic returns.

Additionally, improved physical and cognitive health supports greater social participation and community engagement among older adults, which in turn enhances quality of life (Fried 2016). Indeed, societal participation may not only increase perceived health but also reduce mortality, cognitive disability, frailty, and prevalence of depression (Fried 2016). Thus, giving older adults the guidelines for healthy aging, this intervention could empower them to contribute to society, benefitting both their quality of life, society and the economy. Furthermore, healthy aging may encourage older adults to reenter or remain in the workforce, potentially increasing annual GDP, thus benefitting the economy (Scott 2021).

A limitation of the present study is that the interventions are performed in relatively healthy older adults, in whom age-related molecular and physiological changes may occur more slowly and baseline biomarker variability may be lower than in diseased populations. Consequently, intervention-induced changes may be modest, particularly in cognitive measures of healthy individuals, and more difficult to detect over the 52-week intervention period despite the comprehensive longitudinal phenotyping performed in the study. Nevertheless, data suggest that muscle function can be significantly and lastingly impacted by strength training as used in this protocol (Gylling et al. 2020).

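### The sample-size paragraph needs 40 to be a total for its power calculation and a per-group number for its dropout allowance, so 240 does not follow from the stated calculation

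*Protocol article*

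**What the plan says.** All of this stands in one paragraph of the protocol article, under Statistical considerations.

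- The contrast that is sized: "primary outcome DNA methylation measured at 52 weeks for the pooled three intervention groups (EXE, TRF, FAX) versus the control group".
- The effect: "Assuming an expected pooled effect size for the intervention groups versus the control group is considerable (Cohen’s d = 1.0".
- The error rates: "With a probability of a Type I and Type II error set at α = 0.05 and β = 0.20, respectively". Whether the test is one- or two-sided is not stated.
- The result: "the estimated sample size was 40 participants allocated in a 1:3 ratio (controls:intervention groups".
- Recruitment: "60 participants will be included in each of the four groups (EXE, TRF, FAX, CON), allowing for a 33% dropout rate".

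The same paragraph cites dropout of 5 to 10% in earlier studies, presents the larger number as cover for a higher rate, and leaves dropouts out of the primary outcome analysis. The retained number is therefore the analysed number. The paragraph gives no other effect size, no power for 160 or 240, and no separate calculation leading to 60 per arm.

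**The concern.** A sample-size paragraph should run as one chain: assumptions give a required number, and the required number inflated for dropout gives the number to recruit. Here the chain breaks between its last two links. The number that comes out of the power calculation is a total for the whole trial. The number that the dropout allowance appears to start from is a number per arm, four times as many people.

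What is at stake is how the trial will be read. The only power statement in print is 80% at a standardised difference of 1.0. A reader who attaches it to the 240 recruited would think that the trial was built to see only very large effects, and would misjudge a null result on the primary outcome. The design as recruited can detect an effect less than half that size. In addition, 240 and the 33% allowance have no stated derivation.

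**Working it through.** **Inputs.** All are from Statistical considerations: d = 1.0 (already standardised, so the quoted SD of about 10% is not needed), alpha 0.05, power 0.80, allocation 1:3, 60 per arm and 240 in total, 33% dropout. My assumption: a two-sided test, since sidedness is not given. The one-sided case is shown as well.

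**1. Reproduce the 40.** For r = 3 intervention participants per control, the normal approximation is

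n(control) = (1 + 1/r)(z₀.₉₇₅ + z₀.₈₀)² / d² = (4/3)(1.960 + 0.842)² / 1² = 10.47,

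which gives 4 × 10.47 = 41.9 in total, or 44 (11:33) when rounded up to whole 1:3 sets. At 10:30 the power is 78.2% by the normal approximation and 76.1% by the exact t-test; at 11:33 the t-test gives 80.1%. One-sided, the formula gives 33.0 in total, or 36 (9:27) in whole sets, and 10:30 has 85.2% power (t-test). So 40 is about right as a total.

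**2. Try the other meanings of 40 in the power statement** (d = 1.0, two-sided 5%, t-test).

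| Meaning of 40 | Sizes compared | Power |
|---|---|---|
| Total | 10 vs 30 | 76.1% |
| Control arm, or every arm, pooled contrast | 40 vs 120 | 99.98% |
| Each of two arms, 1:1 | 40 vs 40 | 99.3% |

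Only the total is near the stated 80%.

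**3. Try the same meanings in the dropout allowance.**

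- 40 per arm: 40 / (1 − 1/3) = 60 per arm; 160 / (1 − 1/3) = 240 in total. This matches.
- 40 in total: 1 − 40/240 = 83% dropout. This does not match 33%.

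**4. Put the two together.** As a total, 40 fits step 1 and fails step 3. As a per-arm number (or as the control arm, 40:120), it fits step 3 and fails step 1. No reading fits both.

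**5. What the actual design gives** (pooled contrast, two-sided 5%, t-test).

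| Scenario | Sizes | Power at d = 1.0 | d detectable with 80% power |
|---|---|---|---|
| 33% dropout | 40 vs 120 | 99.98% | 0.515 |
| 10% dropout | 54 vs 162 | > 99.99% | 0.442 |
| 5% dropout | 57 vs 171 | > 99.99% | 0.430 |
| No dropout | 60 vs 180 | > 99.99% | 0.419 |

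Hand check by the normal approximation: d = 2.802 × √(1/40 + 1/120) = 2.802 × 0.1826 = 0.51, and d = 2.802 × √(1/60 + 1/180) = 2.802 × 0.1491 = 0.42.

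**The case against.** The best defence is that the article nowhere says that 40 per arm is required. It reports a calculation and then chooses a larger number as a precaution. Taken literally, losing a third of 240 leaves 160, well above 40, so the allowance is true, if generous. That the per-arm meaning is inferred is correct and should be said. But on the literal reading the 33% is tied to nothing: measured against a requirement of 40 the margin is 83%, and no reason is given for 60 per arm. The step is then unexplained rather than contradictory, and the 80% still does not describe the trial being run.

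It can also be said that the error is in the safe direction and changes nothing in the conduct of the trial. That stands, and it limits the weight of the point.

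Some stronger readings are tempting, and the document does not support them.

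- *That 40 is itself a miscalculation and should be 44.* No test, sidedness or rounding rule is given, the normal approximation gives 41.9, and a gap of two to four people is immaterial beside 240.
- *That the Discussion contradicts d = 1.0.* It says "Consequently, intervention-induced changes may be modest", particularly in cognitive measures, and gives no figure for the primary outcome. It also says that biomarker variability may be lower in this population, which would raise a standardised effect for a given raw change. There is some tension with calling the effect considerable, but no numerical conflict, so the document gives no ground for telling the sponsor to abandon d = 1.0.
- *That the detectable effects can be turned into percentages with the SD of about 10%.* That SD is given for epigenetic prediction of biological age, and the document does not show that it applies to a pace-of-aging score.
- *That power for each arm against control, with a multiplicity adjustment, must be added.* That is a separate question, which an analysis plan not shown here may address.

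**Conclusion.** The point holds as an internal inconsistency in the sample-size justification. The 40 fits the power calculation only as a total, and it fits the 33% allowance only as a number per arm, so 240 and the 33% do not follow from the calculation given. The stated 80% power at d = 1.0 applies neither to the retained nor to the recruited trial. Both have more than 99.9% power at that effect, and their 80% point lies at d of about 0.51 to 0.52 (40 vs 120) and about 0.42 (60 vs 180).

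These figures assume a two-sided 5% test of two means for the pooled contrast, equal SDs, and dropout spread evenly over the arms. The mismatch itself does not depend on sidedness, since 40 is far from a per-arm requirement at d = 1.0 either way.

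A reader might infer that the trial is underpowered for its pooled primary contrast. On the stated assumptions the reverse is true. This should be corrected, but it does not threaten the conduct of the trial.

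**What to change.** Label the 40 as a total, or remove it, and justify the number that is actually recruited. For example:

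> 240 participants are randomised, 60 per arm. With 33% dropout (40 controls, 120 intervention) the pooled contrast has 80% power at two-sided alpha 0.05 for d of about 0.51 to 0.52; without dropout (60 and 180) it has 80% power for d of about 0.42.

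If the sponsor had another reason for 60 per arm, that reason should be stated in place of the link to the d = 1.0 calculation. State the sidedness of the test as well.

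Cost: text only. Recruitment, allocation and the analysis stay as they are.

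### The primary analysis excludes undefined dropouts, so the 52-week randomised contrast can be biased in a direction and size that the protocol does not fix

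*Protocol article*

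**What the plan says.** The rule is in the protocol article, Statistical considerations: "Data from dropouts will not be included in the primary outcomes but may be used in exploratory outcomes". It carries no qualification. Nowhere does the article mention an analysis of all randomised participants, a missing-data method or a sensitivity analysis that would offset it.

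The same paragraph sets the scale of loss that the design tolerates: "60 participants will be included in each of the four groups (EXE, TRF, FAX, CON), allowing for a 33% dropout rate". It also reports that a 3-month pilot and a one-year training study "showed low dropout rates around 5–10" per cent.

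The sample size is based on methylation at 52 weeks, with EXE, TRF and FAX pooled against control. Table 2 schedules the same measurement at baseline, 3 months, 6 months and 1 year.

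Under Interventions, EXE and FAX have two supervised strength sessions and two home cardio sessions a week. TRF and FAX have a daily 16-hour fast. Control has neither.

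**The concern.** Randomisation makes the arms comparable at entry. Removing people because of something that happens afterwards keeps that comparability only if leaving is unrelated to outcome, or related to it in the same way and to the same extent in every arm. Here the demands on participants differ between arms, so both the amount of dropout and the kind of person who drops out may differ.

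The term is also undefined, and its two natural meanings lead to different analyses:

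- **Stopping the intervention.** People who stop but still give a 52-week sample are taken out of the primary comparison.
- **Having no 52-week sample.** The analysis is complete-case. Methylation values at 3 and 6 months from people who left later do not contribute to the primary result, although the sentence allows them exploratory use.

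At stake are the type I error and the interpretation of the primary comparison, plus some precision.

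**Working it through.** **The plan's own figure.** 40/(1 − 0.33) = 59.7, so 60 per group and 4 × 60 = 240. This reproduces the recruitment target if 40 is read as a number per group. (The text presents 40 as the sample size at 1:3 allocation, which is a separate matter.)

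**Inputs from the protocol.** 180 intervention and 60 control participants; α = 0.05, taken as two-sided because sidedness is not stated; 33% dropout allowed for; 5–10% seen in earlier studies.

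**Inputs assumed.** No true effect; the dropout split between interventions and control; the gap g, in SD units, by which dropouts would have scored worse than completers in the same arm; no baseline adjustment.

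**Bias.** If a fraction d of an arm drops out and would have scored g worse, the completers' mean is better than the whole arm's mean by d × g. Hence, towards the interventions:

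bias = d_int × g_int − d_ctrl × g_ctrl

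**Standard error** among completers, in SD units:

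SE = √[1/(180(1 − d_int)) + 1/(60(1 − d_ctrl))]

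**Type I error** (normal approximation) = 1 − Φ(1.96 − bias/SE) + Φ(−1.96 − bias/SE).

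Worked case, 33% versus 10%, g = 0.5 in both: bias = 0.5 × (0.33 − 0.10) = 0.115. SE = √(1/120.6 + 1/54) = 0.164. Bias/SE = 0.70, so type I error = 10.8%. People removed: 0.33 × 180 + 0.10 × 60 = 59.4 + 6, about 65.

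| Dropout, interventions vs control | Gap g | Bias (SD) | Type I error |
|---|---|---|---|
| 10% vs 5% | 0.5 in both | 0.025 | 5.3% |
| 15% vs 5% | 0.5 in both | 0.05 | 6.2% |
| 33% vs 10% | 0.5 in both | 0.115 | 10.8% |
| 33% vs 10% | 1.0 in both | 0.23 | 29% |
| 33% in all arms | equal in both | 0 | 5% |
| 33% in all arms | 0.5 in interventions, 0 in control | 0.165 | 14.8% |

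The last two rows show that equal dropout removes the bias only if dropouts differ from completers by the same amount in each arm.

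**Precision.** Detectable d at 80% power = (1.96 + 0.84) × √(1/n_ctrl + 1/n_int). With everyone analysed (60 and 180) it is 0.42. With completers at 33% dropout (about 40 and 120) it is 0.51. At the plan's d = 1.0, power exceeds 99.9% either way, so power gives no reason to exclude anyone.

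**The case against.** The strongest reply is that dropout probably means leaving the trial. Under Biweekly phone calls, the protocol treats help with adherence separately from withdrawal: "there will not be applied pressure on individuals to continue their enrollment if they wish to withdraw from the trial". No adherence criterion for the primary analysis appears anywhere. On that reading, poor adherers who attend at 52 weeks stay in their allocated arm. This stands as far as it goes. A reader might infer that the contrast is between adherent intervention participants and nearly all controls, but the protocol does not say so. What remains is a complete-case rule, which is still open to bias.

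A second reply concerns size. The protocol expects little dropout and offers 33% as a margin. At 10% versus 5% the inflation is trivial. The 29% figure needs a gap of 1.0 SD, as large as the whole effect on which the trial is sized. Adjusting for baseline methylation could shrink the bias further. All of this stands, and the higher figures should be read as stress cases.

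Three further inferences are tempting but unsupported:

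- **That the bias favours the interventions.** It does in the scenarios above because they assume it. The documents fix no direction, and it could go the other way.
- **That most dropouts have usable follow-up data.** The timing of dropout is not given, and those who leave before month 3 have only a baseline value.
- **That a loss of 80 people goes with the inflated error rates.** A loss of about 80 of 240 means roughly 33% in every arm, where equal gaps give no bias.

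Nor are controls free of burden: they have the same test battery, activity monitors and biweekly calls.

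Finally, an unseen analysis plan may say more. But the article states the exclusion as a rule, so a plan that analysed everyone randomised would contradict it.

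**Conclusion.** The point holds. The protocol excludes an undefined group from the primary outcome on a post-randomisation event, and nothing in it offsets this. The pooled 52-week contrast can therefore be biased, in a direction and by an amount that the documents do not determine.

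If dropouts would have scored worse and more of them leave the intervention arms, the type I error ranges from negligible inflation at the dropout seen in earlier studies to roughly double the nominal level near the planned allowance with a 0.5 SD gap. The 29% case is an extreme. If dropout and gaps are equal across arms, there is no bias, only a loss of precision.

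The case for changing the rule does not rest on the larger figures. The rule decides who counts in the primary randomised comparison, and exclusion brings no gain.

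**What to change.** Replace the sentence with wording to this effect:

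- The primary analysis includes all randomised participants in their allocated arm and uses all available methylation values at baseline, 3, 6 and 12 months. One suitable method is a mixed model for repeated measures with baseline value and sex (the stratification factor) as covariates; the details can sit in the analysis plan.
- Dropout is defined, with stopping the intervention kept distinct from leaving the trial. Participants who stop the intervention but do not withdraw consent are still invited to the scheduled 52-week sample.
- The completers analysis is supplementary.
- A sensitivity analysis allows for values missing not at random, for example delta-adjusted imputation. The mixed model does not by itself protect against that.

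The cost is a wording change and slightly more analysis work. The visits are already in Table 2, although some people whom the current rule might not have sampled at 52 weeks would now be sampled. The estimate may be less favourable than in completers. The change should be made before outcome data are analysed, so that it cannot look data-driven.
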